### 3.3.3 Interruption or Discontinuation of Treatment

Before interrupting or discontinuing study drug, the investigator must contact the sponsor or designee (except in the case of an emergency) to discuss the proposed reason. It will be documented whether or not each subject completed the clinical study. If any subject's study treatment or observations were discontinued, the reason will be recorded. Reasons that a subject may discontinue participation in this clinical study may be one or more of the following:

- Adverse event(s)
- Abnormal laboratory value(s)
  - Hemoglobin: decrease below 9.0 gm/dL
  - AST:  $\geq 3 \times$  ULN (upper limit of normal)
  - ALT:  $\geq 3 \times$  ULN
  - LDH:  $\geq 3 \times$  ULN
  - Alkaline Phosphatase:  $\geq 2 \times$  ULN
  - Triglyceride:  $\geq 1000$  mg/L
  - Creatinine:  $>2$  mg/dL
- **Any fasting glucose  $>300$  mg/dL and/or any HbA1c value of  $>12\%$  in spite of ad lib adjustments to oral hypoglycemic agents and/or insulin dosage.**
- Subject withdrew consent
- Lack of compliance to protocol requirements and/or procedures
- Lost to follow-up

- Administrative deviations which preclude satisfactory completion of protocol assessments

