#### **Exclusion criteria**

1. Serum creatinine >2 mg/dL;
2. Fasting triglyceride >1000 mg/dL;
3. Albuminuria >200 mcg/24 hours (this assessment may be obtained during the lead-in period);
4. Positive mammography (if female) or prostate-specific antigen (PSA) or prostate examination for cancer (if male);
5. Donation of blood during the 30 days prior to the screening visit. Donation of blood is also prohibited during the study;
6. Use of oral or parenteral glucocorticoids in the 30 days prior to screening;
7. Use of any experimental or marketed growth hormone (GH), GH secretagogues (e.g., growth hormone releasing factor (GRF) products), IGF-1, or IGFBP-3 during the previous 6 months;
8. Subjects with two or more severe hypoglycemia episodes within the past 6 months, or any hospitalization or emergency room visit due to poor glycemic control within the past 6 months. Similarly, during the lead-in period, any subject with more than one severe hypoglycemic episode or any hospitalization or emergency room visit due to poor glycemic control will be excluded from randomization;
9. History of or presence of active concomitant conditions or diseases (e.g., myocardial infarction, poorly controlled hypertension, thyroid disease, rheumatoid arthritis, seizure disorder, diabetic neuropathy, diabetic retinopathy [except patients

with only microaneurysms on fundus examination]) that would interfere with the protocol conduct and endpoint measurements;

10. Subjects with a major surgical operation during the 30 days prior to screening;
11. Subjects with known hypopituitarism, history of pituitary tumor/surgery, head irradiation, or severe head trauma.
12. Current cancer or history of cancer, except non-melanomatous skin cancer;
13. Subjects with active infection at any body site or a history of severe infection (requiring oral or parenteral treatment) during the 30 days prior to screening;
14. Subjects with drug or alcohol dependence or abuse;
15. Subjects with clinically significant abnormalities on screening laboratory evaluation (unless discussed with and approved by the medical monitor);
16. Subjects with allergy to synthetic growth hormone products or their excipients;
17. Subjects who have previously received growth hormones in any clinical trial; and
18. Participation in a trial of an experimental drug or device within 90 days prior to screening.

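### Protocol Section 3.3.3 prints the triglyceride discontinuation value in mg/L, which makes it one tenth of the entry limit; very probably a slip for mg/dL

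*Protocol*

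**What the plan says.** Triglyceride limits appear in two places in the Protocol.

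- **Entry (Section 3.3.2, exclusion criterion 2):** "Fasting triglyceride >1000 mg/dL". Patients up to and including 1000 mg/dL pass this criterion.
- **Discontinuation (Section 3.3.3, abnormal laboratory values):** "Triglyceride: $\geq 1000$ mg/L".

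The other concentrations in the Section 3.3.3 list are "Hemoglobin: decrease below 9.0 gm/dL", "Creatinine: $>2$ mg/dL" and "Any fasting glucose $>300$ mg/dL", all per dL.

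Two sentences in Section 3.3.3 set the force of the list. It is introduced by "Reasons that a subject may discontinue participation in this clinical study may be one or more of the following", and before treatment is interrupted or stopped "the investigator must contact the sponsor or designee (except in the case of an emergency) to discuss the proposed reason".

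Exclusion criterion 15 also bears on entry. It covers "Subjects with clinically significant abnormalities on screening laboratory evaluation (unless discussed with and approved by the medical monitor").

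**The concern.** The discontinuation value should mark a change for the worse from what was acceptable at entry. Read literally, this one sits far below the entry limit. A patient can pass the triglyceride criterion and meet the discontinuation value on the same blood sample, so the line cannot tell a new abnormality from a value that was acceptable at entry.

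The visit schedule in Section 3.5.1 makes this concrete. A lipid profile is drawn at Visit 3, the visit at which the first dose is given, so a patient can meet the printed value at baseline. It is drawn again at Weeks 1, 4 and 8 while dosing continues. Sites could then diverge, some following the text and others silently reading mg/dL. With 15 patients randomized per group so that about 13 complete (Sections 3.3.1 and 4.1.5), there is little room for avoidable discontinuations.

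**Working it through.** **Inputs**

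| Item | Printed limit | Protocol section |
|---|---|---|
| Triglyceride, entry | excluded if >1000 mg/dL | 3.3.2, exclusion 2 |
| Triglyceride, discontinuation | ≥1000 mg/L | 3.3.3 |
| Creatinine, entry | excluded if >2 mg/dL | 3.3.2, exclusion 1 |
| Creatinine, discontinuation | >2 mg/dL | 3.3.3 |
| Hemoglobin, discontinuation | <9.0 g/dL | 3.3.3 |
| Fasting glucose, discontinuation | >300 mg/dL | 3.3.3 |

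**Step 1: common unit.** 1 L = 10 dL, so x mg/L = x/10 mg/dL. The printed discontinuation value is 1000/10 = 100 mg/dL.

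**Step 2: ratio to the entry limit.** 100/1000 = 0.1, a tenfold difference.

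**Step 3: overlap.** Criterion 2 is passed at ≤1000 mg/dL, and the printed discontinuation value is met at ≥100 mg/dL. Both hold from 100 to 1000 mg/dL. This is an upper bound on the range of eligible patients affected, because criterion 15 may exclude some of them.

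**Step 4: slip or deliberate lower limit?**

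- The number 1000 is the same at entry and at discontinuation; only the unit differs.
- Creatinine is the other analyte with a concentration limit in both lists, and its two limits agree in number and unit.
- The other three concentrations in Section 3.3.3 are per dL.
- Counting every printing of a blood-concentration limit in the Protocol, the per-dL ones are 2 in Section 3.3.2 (creatinine, triglyceride), 3 in Section 3.3.3 (hemoglobin, creatinine, fasting glucose) and 5 of the 250 mg/dL home-glucose call-in value (Visit 3, Visit 4, Visits 5 and 6, Visit 7, and Section 3.5.2.3.7). That is 2 + 3 + 5 = 10 per dL. The triglyceride line in Section 3.3.3 is the only one per L.
- Nothing elsewhere in the Protocol restates the triglyceride value or explains a per-litre unit.

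**Step 5: with the unit corrected.** The discontinuation value becomes ≥1000 mg/dL and its ratio to the entry limit is 1000/1000 = 1. Values from 100 to just below 1000 mg/dL no longer meet it.

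The share of patients who would fall between 100 and 1000 mg/dL cannot be computed, because the Protocol gives no triglyceride distribution.

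**The case against.** The strongest objection is that the slip is so evident that it does little harm. The list gives possible reasons for discontinuation, not automatic stopping rules. A triglyceride of a few hundred mg/dL is not an emergency, so the investigator would have to speak to the sponsor first, and the mismatch would probably surface in that call. The evidence that mg/dL was meant would also lead many site readers to read it that way. The error is on the cautious side: it flags too early and hides no high value. Criterion 15 can remove some of the affected patients at screening.

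All of this is right as to consequence, and it keeps the point a modest one. None of it makes the printed value correct. A limit that works only if readers disregard its unit is not usable as written, and criterion 15 is a judgment the medical monitor can waive, so it does not reconcile the two limits.

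Two smaller objections remain. The text was extracted from a PDF, so a lost letter cannot be fully excluded, although the mg/dL units elsewhere in the same list were read correctly. And no calculation in the Protocol is wrong here; this is a unit inconsistency between two sections. Neither changes the correction.

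**Conclusion.** The line is wrong as written. The printed triglyceride discontinuation value is 100 mg/dL against an entry limit of 1000 mg/dL, and no other text reconciles them. That mg/dL was intended is an inference, but a well-supported one. The tenfold ratio follows from the printed figures alone; the 100 to 1000 mg/dL overlap is an upper bound because of criterion 15. No hypothesis, endpoint or sample-size figure is affected. It should be fixed because it is a decision threshold for patient safety and the correction is almost free.

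**What to change.** In Section 3.3.3, change the unit only, so that the line reads: Triglyceride: ≥1000 mg/dL. The sponsor's medical team should confirm the value.

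With that wording a patient at exactly 1000 mg/dL would still be eligible and also meet the discontinuation value, because entry excludes above 1000 and discontinuation starts at 1000. This is trivial in practice, and the medical team can accept it or settle it in the same confirmation.

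The cost is a one-line protocol correction, with no change to the design, the visits or the analysis.

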### 3.4. Treatment

#### 3.4.1 Investigational Drug and Reference Therapy

Active drug and placebo will be provided as lyophilized powder in vials of identical appearance and supplied in blister cards at each monthly visit. The active drug is supplied as 1.1 mg of TH9507 (peptide content) with 55 mg of mannitol. The placebo is composed of 55 mg of mannitol. The study drugs will be supplied as follows:

| Dose | No. of Vial of Active Drug
(A) | No. of Vial of Placebo
(B) |
|-------------|-------------------------------------------|---------------------------------------|
| 1 mg        | 1 vial of 1.1 mg active drug              | 1 vial of mannitol                    |
| 2 mg        | 2 vials of 1.1 mg active drug             | -                                     |
| Placebo     | -                                         | 2 vials of mannitol                   |

Each vial will be reconstituted with 1.1 mL of sterile water for injection (provided by the sponsor). One mL of each preparation is then taken out of each vial using a 3-mL syringe. The total volume will be 2 mL. The preparation is then injected subcutaneously.

The lyophilized vials will be kept at -20°C at the investigational sites. The supplies of study drug dispensed to the subjects will be kept refrigerated between 2°C and 8°C at the subject's home for daily reconstitution and use.

Subjects will self-inject 2 mL of study drug subcutaneously (using 1 mL each from vial A and vial B) at rotating sites every morning at 9:00AM  $\pm$  3 hour, (i.e., between 6AM and noon). The subject may elect to have a family member or a health professional administer the study drug. The study drug may be administered in either one or two subcutaneous injections at each dosing time at one or two sites. The study drug will be administered at the General Clinical Research Centers (GCRCs) at Visits 3, 4, 5, and 6.

Medication labels will comply with the regulatory requirements.

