## 3. Investigational Plan

### 3.1 Overall Study Design

This is a randomized, double-blind, placebo-controlled, parallel group, multicenter study of two doses of TH9507 (1 mg and 2 mg) administered daily by subcutaneous injection for 12 weeks.

After screening and a 14-day lead-in period, subjects will be randomized by insulin use (see Section 4.1.6) to one of three treatment groups. Subjects will be evaluated after 1, 4, 8, and 12 weeks of treatment and at a follow-up visit at Week 16.

The study schematic is presented in Figure 3.1-1.

Figure 3.1-1 Study Schematic

[figure not shown]

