#### VISIT 4: (Week 1 ± 1 day; Treatment Period)

- Assess adverse events.
- Review concomitant medications.
- Return all used and unused study drugs.
- Obtain body weight.
- Obtain vital signs (BP, RR, PR).
- Review/dispense diary.
- Download home glucose readings from previous 6-8 days.
- Replenish boxes of strips and lancets, if necessary.
- Collect 24-hour urine for creatinine and nitrogen.
- Obtain blood (fasting) for laboratory tests – IGF-1, IGFBP-1, IGFBP-3, lipid profile, hematology, chemistry.
- Perform oral 3-hr GTT with 75Gm Glucose (Glucola).
- Obtain blood for insulin and glucose levels every 30 minutes during OGTT.
- Administer blinded study drug while in clinic at approximately noon.
- Dispense study drug supply for three (3) weeks (24 doses).

- **Remind the subjects to call the clinic for any home blood glucose value that is >250 mg/dL.**
- Instruct the subject to withhold oral sulfonylurea, insulin, and other insulin secretagogues but he/she may take oral non-sulfonylurea hypoglycemic medication (if oral insulin sensitizer) in the morning of Visit 4.
- Instruct the subject to collect urine the day before the scheduled visit (starting at 6AM) until the morning (6AM) of the clinic visit.
- Schedule Visit 5 to occur 19-23 days after Visit 4.

VISIT 5 and VISIT 6: (Week 4  $\pm$  2 days and Week 8  $\pm$  3 days, Treatment period)

- Assess adverse events.
- Review concomitant medications.
- Return all used and unused study drugs.
- Obtain body weight.
- Obtain vital signs (BP, RR, PR).
- Dietician interview and assessment – caloric intake assessment, skin thickness (Harpenden) , body fat mass (Lange); and waist/hip measurements.
- Review/dispense diary.
- Download home glucose readings for the period since the previous visit.
- Collect 24-hour urine for creatinine and nitrogen.
- Obtain blood for laboratory tests – IGF-1, IGFBP-1, IGFBP-3, lipid profile, hematology, chemistry, HbA1C.
- Perform oral 3-hr GTT with 75Gm Glucose (Glucola).
- Obtain blood for insulin and glucose levels every 30 minutes during OGTT.
- Administer daily dose of blinded study drug in clinic at approximately noon.
- Dispense study drug supply sufficient for four weeks (32 doses).
- Replenish boxes of strips and lancets, if necessary
- **Remind the subjects to call the clinic for any home blood glucose value that is >250 mg/dL.**

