- Instruct the subject to withhold oral sulfonylurea, insulin, and other insulin secretagogues but he/she may take oral non-sulfonylurea hypoglycemic medication (if oral insulin sensitizer) in the morning of Visit 6 and Visit 7.
- Instruct the subject to collect urine the day before the scheduled visit (starting at 6AM) until the morning (6AM) of the clinic visit.
- Schedule Visit 6 to occur 25-31 days following Visit 5, OR
- Schedule Visit 7 to occur 25-31 days following Visit 6.

VISIT 7: (Week 12  $\pm$  3 days)

- Assess adverse events.
- Review concomitant medications.

- Return all used and unused study drugs.
- Obtain body weight.
- Obtain vital signs (BP, RR, PR).
- Determine body mass index.
- Perform funduscopy with dilation by optometrist or ophthalmologist (may be performed within 5 days of date of Visit 7).
- Perform physical/neurological examinations (including examination for diabetic sensory neuropathy).
- Review/dispense diary.
- Download home glucose readings from previous 4 weeks.
- Dietician interview and assessment – caloric intake assessment, skin thickness (Harpender), waist/hip measurements, and body fat mass (Lange).
- Collect 24-hour urine for creatinine and nitrogen.
- Obtain blood (fasting) for laboratory tests – IGF-1, IGFBP-1, IGFBP-3, serum for TH9507 antibody, lipid profile, hematology, chemistry, HbA1C.
- Perform oral 3-hr GTT with 75Gm Glucose (Glucola).
- Obtain blood for insulin and glucose levels every 30 minutes during OGTT
- **Remind the subjects to call the clinic for any home blood glucose value that is >250 mg/dL.**
- **Investigator completes global assessment of diabetes control**
- Replenish boxes of strips and lancets, if necessary
- Subject receives NO STUDY DRUG AT THIS VISIT.
- Schedule Visit 8 (Post-treatment Visit) to occur 25-31 days following Visit 7.

VISIT 8: (Week 16 ± 3 days; Follow-up Visit; 16 weeks after randomization; 4 weeks post-treatment)

- Assess adverse events.
- Review concomitant medications
- Obtain body weight.
- Obtain vital signs (BP, RR, PR).
- Obtain blood for laboratory tests (hematology; blood chemistry; lipid profile)
- Collect urine for urinalysis.
- Schedule mammography (for females) and prostate examination/PSA (for males).
- Dietician interview and assessment – caloric intake assessment, skin thickness (Harpender) , body fat mass (Lange), and waist/hip measurements.
- Review diary.
- Download home glucose readings for the period since Visit 7.

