#### 3.5.2.3.6 Oral Glucose Tolerance Test (OGTT) with paired glucose and insulin levels

Blood glucose and insulin will be measured at 0 minutes (prior to ingestion of glucose), 30 minutes, 1, 1.5, 2, 2.5, and 3 hours. For these determinations, oral sulfonylureas, insulin, and other insulin secretagogues must be withheld on the morning of the OGTT. Insulin sensitizers need not be withheld at such times.

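### The protocol does not say how study drug is handled on OGTT mornings: the every-morning home dose is not reconciled with the noon clinic dose at Visits 4 to 6, and the home dose on the morning of Visit 7 (Week 12) is not addressed

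*Protocol*

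**What the plan says.** **Home dosing.** Section 3.4.1 tells subjects to self-inject "at rotating sites every morning at 9:00AM", with a tolerance that it spells out as "i.e., between 6AM and noon". That sentence makes no exception for visit days. Section 3.1 describes the drug as "administered daily by subcutaneous injection for 12 weeks".

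**Clinic dosing.** The same paragraph of 3.4.1 adds: "The study drug will be administered at the General Clinical Research Centers (GCRCs) at Visits 3, 4, 5, and 6". In section 3.5.1, the Visit 4 list has "Administer blinded study drug while in clinic at approximately noon" and the list for Visits 5 and 6 has "Administer daily dose of blinded study drug in clinic at approximately noon". Both items come after the 3-hour OGTT in their lists. The Visit 7 list has "Subject receives NO STUDY DRUG AT THIS VISIT" and also includes an OGTT.

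**What is withheld before an OGTT.** Section 3.5.2.3.6 says that sulfonylureas, "insulin, and other insulin secretagogues must be withheld on the morning of the OGTT". The subject instructions in the lists for Visit 2, Visit 4, and Visits 5 and 6 name the same drug classes. None of them mentions study drug.

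**What the OGTT feeds.** Section 4.1.1 builds the primary endpoint from basal insulin and the 30-minute insulin and glucose increments. Section 4.1.4 compares the change from baseline at Week 12 across the three groups.

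**The concern.** The protocol gives two dosing instructions for the same morning and does not say how they fit together. It issues an explicit list of drugs to hold before the OGTT, and study drug is not on it. A subject who follows the home rule and the hold list to the letter could inject at home, take the OGTT, and then receive the clinic dose. A subject who understands the clinic dose to be that day's dose would take the OGTT about a day after the previous injection.

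Two things are at stake. One is safety: the wording permits a home and a clinic dose on the same day at Visits 4, 5 and 6. The other is the primary endpoint: the interval from last dose to OGTT is not fixed, and it could differ between subjects and between visits. The baseline OGTT at Visit 3 precedes all study drug, and placebo subjects receive no active drug. Any effect of dose timing would therefore appear only in the post-baseline values of the two active arms.

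**Working it through.** The plan states no figure to reproduce. The check sets the passages side by side, then does simple timing and supply arithmetic.

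**Step 1. Visit by visit.**

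| Visit | OGTT | Clinic dose | Home dose that morning |
|---|---|---|---|
| 3 (Week 0) | yes | first dose, about noon | not possible, no drug dispensed yet |
| 4 (Week 1) | yes | about noon, not called the daily dose | general rule applies, no exception stated |
| 5, 6 (Weeks 4, 8) | yes | about noon, called the daily dose | general rule applies, no exception stated |
| 7 (Week 12) | yes | none | not addressed |

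The same-day double dose is thus possible at three visits only (4, 5 and 6). The undefined dose-to-test interval affects all four post-baseline OGTTs.

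**Step 2. Dose-to-OGTT interval.** The OGTT start time is not given. Assume 9AM, so that a 3-hour test ends at noon, when the clinic dose is due.

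- Home dose taken that morning at 6AM: 9 − 6 = 3 h before the OGTT and 12 − 6 = 6 h before the clinic dose.
- Home dose taken that morning at 9AM: 9 − 9 = 0 h before the OGTT and 12 − 9 = 3 h before the clinic dose.
- No home dose that morning, last dose the previous day at 6AM: 18 + 9 = 27 h.
- No home dose that morning, last dose the previous day at noon: 12 + 9 = 21 h.

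The two groups of intervals are 0 to 3 h and 21 to 27 h. With an 8:30AM start they become 0 to 2.5 h and 20.5 to 26.5 h.

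**Step 3. Does the supply prevent a home dose on the visit morning?** Let D be the days to the next visit, from the scheduling windows in 3.5.1. Doses needed from the kit are:

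- D − 1 if no home dose is taken on the next visit's morning and clinic doses come from separate stock;
- D if only one of those two conditions holds;
- D + 1 if a home dose is taken that morning and the clinic dose on the dispensing day comes from the kit.

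| Interval | Dispensed | D | D − 1 | D | D + 1 |
|---|---|---|---|---|---|
| Visit 3 to 4 | 8 | 6–8 | 5–7 | 6–8 | 7–9 |
| Visit 4 to 5 | 24 | 19–23 | 18–22 | 19–23 | 20–24 |
| Visit 5 to 6, and 6 to 7 | 32 | 25–31 | 24–30 | 25–31 | 26–32 |

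Only one combination runs short: Visit 3 to 4 at 8 days in the last case (9 needed, 8 supplied). In every other combination a dose is available on the visit morning, so supply does not settle the question.

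**Step 4. Visit 7.** Twelve weeks of daily dosing from day 0 is 12 × 7 = 84 doses, on days 0 to 83. Nominal Visit 7 is day 84, which would put the last dose on the day before. The ±3-day window places the actual visit anywhere from day 81 to day 87, so the count alone does not tell a given subject whether to inject that morning.

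**The case against.** The strongest reply is that the protocol, read as a whole, prescribes one dose a day. A general rule is followed in the same paragraph by a specific statement of where the drug is given at named visits. Visits 5 and 6 call the clinic dose the daily dose. The regimen is daily throughout, and noon lies at the edge of the home window. This is a good argument and it stands as to intent at Visits 4 to 6. A reader might infer that the protocol orders two doses on visit days. It does not, and the passages are ambiguous rather than in direct contradiction.

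On Visit 7, the structure suggests that treatment has ended by then. Its heading lacks the treatment-period label that Visits 4 to 6 carry, and Visit 8 is described as four weeks post-treatment. That makes a home dose less likely but does not rule one out. The item in the Visit 7 list speaks only of drug received at the visit.

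The spare doses are not themselves a fault. They cover the visit windows, and their number depends on where clinic doses come from. Returned vials and the diary could reveal an extra dose. Vial counts do not give the time of a dose, however, and the expected count depends on the rule that is missing.

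A reader might also use the 8-hour half-life in section 1 to argue that the two kinds of OGTT differ greatly in drug exposure, and hence in the endpoint. The figure is an in-vitro plasma value, and nothing in the protocol links exposure at the time of the test to the relative insulin response.

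Finally, Appendix 1 and section 6 are not shown and the consent pages were removed. An instruction to subjects could sit there. If so, 3.4.1, 3.5.1 and 3.5.2.3.6 would still need to agree with it.

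**Conclusion.** The point holds as an unresolved ambiguity that reaches the primary endpoint. The likely intent at Visits 4 to 6 is one dose, given in clinic after the OGTT, but no text shown says so and the hold instructions omit study drug. On that charitable reading Weeks 1, 4 and 8 are pre-dose tests, while Week 12, on which section 4.1.4 rests the comparison, has neither a clinic dose nor a rule for the home dose.

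In size, the wording permits a same-day double dose on up to three visits per subject. It also leaves the dose-to-test interval open at four OGTTs, at about 0 to 3 h or 21 to 27 h. These intervals assume a 9AM start and dosing within the stated window. How many subjects would take the literal reading is unknown. Any resulting bias or loss of power cannot be derived from the protocol, and none is claimed here.

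**What to change.** Reconcile section 3.4.1 with the Visit 4 to 7 lists in 3.5.1, with the pre-visit instructions in the Visit 2, Visit 4, and Visit 5 and 6 lists, and with 3.5.2.3.6. Study-drug handling on the morning of each OGTT, including Visit 7, should be stated once and consistently, and it should appear beside the existing instruction on glucose-lowering drugs. The choice of rule is the sponsor's.

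Record on the CRF the date and time of the last study-drug dose before each OGTT. The diary already covers study-drug administration, so this adds little work, and it lets the analysis describe the dose-to-test interval by arm and visit.

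The cost is a few sentences in the protocol and subject instructions and one CRF field, with no added visits, samples or subjects.
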